#### Patient reported outcomes

Participants receive the UNBLOCS Symptoms/Surgery Questionnaire at baseline in clinic, 6 weeks post-surgery (by post), and at 3 and 12 months post-surgery in clinic (with the option to take home and return in pre-paid envelope if preferred). The questionnaire contains questions from standardised outcome instruments for urinary and sexual symptoms (listed in Fig. 2) and the baseline questionnaire had versions for men who were using a catheter and those who were not, as some items were not relevant for catheterised patients. Participants who are catheterised at the time of the 3- or 12-month questionnaires are instructed to only answer the questions that they feel able to. The Bladder Diary was given to participants at their baseline clinic and at their 3 and 12 months clinics if they do not require a catheter to void at the time. The Bladder Diary is used to record fluid intake, frequency and volume of micturition and bladder sensation and use of pads over 3 days, and is returned in a pre-paid envelope.

#### Economic data collection

Details of initial hospital stay resource use, e.g. operation duration; operating staff; consumables; the time spent in recovery; length of stay on different wards; overall length of stay and treatment for complications, were collected on study-designed case report forms (CRFs) by the research nurse at the time of the inpatient/day-case stay for the initial surgery. Hospital patient-linked information costing systems are used if available to capture follow-up hospital use at the treating hospital. If this information cannot be accessed then subsequent inpatient stays, outpatient visits and procedures occurring at the treating hospitals are abstracted from the patients’ medical records and recorded on a CRF.

On discharge from hospital, and at 3 months follow-up the patients are given a study designed Resource Use Log (RUL) to be used as an aide memoire in which to record NHS and private community-based health care use, other NHS hospital health care use, medications, personal social service (PSS) resource use in addition to travel, time off work/usual activities and any other expenses resulting from their treatment [11]. These logs reflect the design of the 3-month and 12-month UNBLOCS Resource Use questionnaire. At 3 months and 12 months follow-up, participants are able to use the information from the RUL in order to complete the UNBLOCS Resource Use Questionnaire, which they take home from clinic, or receive by post along with a pre-paid return envelope. The EQ-5D-5L will be used to calculate quality-adjusted life years (QALYs). The new five-level EQ-5D is used in preference to the three-level one, owing to its improved discriminatory power [12].

#### Qualitative data collection

The main aims of the qualitative component, which is being investigated with in-depth semi-structured interviews with participants at between 3 and 6 months post-surgery are:To explore patient experiences of ThuVARP and TURPTo explore determinants of patient satisfaction with the two proceduresTo identify any differences in experience between men presenting with LUTS or urinary retention.

The basis of the interview schedule/topic guide is focused around these three themes and further informed by the literature and clinical experience of the co-applicants, but will also allow participants to address issues or concerns of particular relevance to their own experience. Interviews have been targeted at 3 to 6 months post-surgery to allow recovery from the operation and return to daily activities whilst also permitting good recall of the experience of the procedures and immediate sequelae.

Participants from both the ThuVARP and TURP intervention arms are recruited to take part in exploratory interviews. Study participants who provide consent to being approached for qualitative interviews are purposively selected to represent the two surgical interventions, two presentations for surgery (LUTS and urinary retention) and demographic characteristics such as age. This is included to better understand the differences between the two surgical procedures in terms of the individuals’ lived experience. In particular, the interview schedule focuses on the immediate experience surrounding surgery and features of the continued recovery and effects on daily life. This is important to capture contextual data to support interpretation and contextualisation of the trial quantitative outcomes.

Participants are also asked to articulate what their expectations of surgery were prior to the procedure and upon which factors they judged their perceived satisfaction, or dissatisfaction subsequent to the operation, and whether this was a dynamic or static decision that altered during the recovery period. This aspect of the investigation will focus on capturing both clinical and non-clinical determinants of satisfaction which will be linked to the quantitative analyses for interpreting the outcomes e.g. quality of life.

### Sample size

This study is powered to establish equivalence in clinical improvement. The Chinese trial [6] observed differences of 0.4 ml/s (95% CI: -2.0 to 2.8) in Qmax and 0.4 units (-0.7 to 1.5) in IPSS between ThuVARP and TURP. Variability (standard deviation; SD) in data at 12 months was approximately 6.0 ml/s (Qmax) and 3.0 units (IPSS), but previous trials of TURP report greater variability, around 9 ml/s (Qmax) and 5 units IPSS [13, 14].

We have specified differences of 4 ml/s in Qmax and 2.5 units in IPSS, as demonstrating equivalence. Equivalence studies often use an alternative hypothesis of a difference of zero between treatments. However, the Chinese trial observed differences of around 0.4 ml/s and 0.4 units for Qmax and IPSS. Incorporating these as alternative hypotheses ensures adequate power to demonstrate equivalence if treatments are indeed similar but not identical.

Assuming SDs of 9 ml/s for Qmax and 5 units for IPSS, the target sample size for patients needed to complete the 12-month follow-up was 163 patients in each group. Using NQuery Advisor, this will provide 85% power to demonstrate equivalence for Qmax and just over 90% power for IPSS, at a two-sided alpha of 5%. Assuming 20% loss to follow-up following randomisation, it was necessary to recruit 410 men in total. This loss to follow-up is a conservative estimate from our experience of previous trials. However, we are aiming to reduce loss to follow-up through letter, text and telephone reminders to patients.

### Randomisation

All men who entered the trial were logged with the central study office and given a unique, six-digit study (participant) identification number.

Participants were randomly allocated to treatment arms using an automated web/telephone randomisation system provided by the Bristol Randomised Trials Collaboration (BRTC). This took place in the anaesthetic room when the patient was anaesthetised.

Randomisation was stratified by centre and whether the patient was eligible due to bothersome LUTS or urinary retention, and random blocking was employed (of two, four and six randomly allocated).

### Blinding

To reduce bias in the assessment of outcomes, participants were not informed of their study arm allocation, although their general practitioner (GP) can access this information. Participants were informed that, although it would be preferred that they did not know which operation they have had; their GP will not be prevented from giving them this information if they request it. We anticipated that some men will ask for, or discover, their allocation at some point during the study and we will be asking them to reveal when and how they became aware of this in the 12-month follow-up questionnaire. Participants will be informed of the type of BPO surgery they received after receipt of their 12-month follow-up questionnaires and Bladder Diary, or 1 month after they have received a reminder for these.

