### Trial design

This is a multicentre, pragmatic, randomised, controlled, parallel-group trial of thulium laser transurethral vaporesection of the prostate (ThuVARP) versus standard transurethral resection of the prostate (TURP) in men with benign prostatic obstruction (BPO). Randomisation is at the patient level so men were randomised 1:1 to receive either ThuVARP or TURP.

This study is powered to establish equivalence in clinical improvement. We are specifying differences in Qmax and IPSS of no greater than 4 ml/s and 2.5 units respectively, as demonstrating equivalence.

Follow-up is at 6 weeks, 3 and 12 months after surgery for the patient-reported outcome (PRO) IPSS, and at 3 and 12 months for the maximum urine flow rate (Qmax), with 12 months being the primary endpoint. Patients are asked to complete other patient-reported outcomes at 6 weeks after surgery (by post), and after 3 and 12 months. The study flow diagram is provided in Fig. 1 and the Standard Protocol Items: Recommendations for Interventional Trials (SPIRIT) checklist in Additional file 1.

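### Allocation may be disclosed one month after a reminder while the 12-month questionnaire is still out, so any IPSS completed after that is an unblinded co-primary outcome

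*Protocol article*

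**What the plan says.** The Blinding section gives the purpose of keeping men uninformed: "To reduce bias in the assessment of outcomes, participants were not informed of their study arm allocation". It then sets two alternative triggers for disclosure by the trial. The first is "Participants will be informed of the type of BPO surgery they received after receipt of their 12-month follow-up questionnaires and Bladder Diary". The second, joined to it by the word 'or', is "or 1 month after they have received a reminder for these".

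The same section expects that some men will find out earlier, and provides for it: "we will be asking them to reveal when and how they became aware of this in the 12-month follow-up questionnaire". It also accepts that a GP may tell a man on request.

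Four other places bear on the point:

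- **Trial design** and **Outcome measures** make IPSS, a patient-reported score, one of two co-primary outcomes, "with 12 months being the primary endpoint".
- **Patient reported outcomes** has the 12-month questionnaire handed out in clinic, but men may take it home and post it back.
- **Sample size** says "we are aiming to reduce loss to follow-up through letter, text and telephone reminders to patients".
- **Statistical analysis** specifies a primary comparison by allocated group with multiple imputation. Its sensitivity analyses cover complete cases, baseline adjustment, surgeon effects, CACE and per protocol. None concerns awareness of allocation.

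**The concern.** For IPSS the patient is the assessor, so blinding the patient is what protects this outcome. The second trigger can only operate when something is still outstanding, and the outstanding item may be the form that carries the co-primary IPSS. The rule does not ask whether the IPSS is in, or whether the form has been closed to further receipt. A man who is reminded, waits a month, is told his operation and then posts his form has rated his symptoms knowing whether he had the laser or the standard procedure.

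What is at stake is a small shift in the IPSS difference. In an equivalence trial either direction matters. A shift toward zero makes equivalence too easy to declare, and a shift away from zero costs power.

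**Working it through.** **Reading the rule**

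1. If all 12-month forms are in, the first trigger applies and the IPSS was completed before disclosure by the trial.
2. If something is outstanding and a reminder has been sent, the second trigger applies one month later. There are then three cases:
   - Only the Bladder Diary is missing. The IPSS is already in, and disclosure does no harm to it.
   - The questionnaire comes back within the month. It was completed before disclosure by the trial.
   - The questionnaire is still out at one month. The man is told. If he then completes and returns it, that IPSS is unblinded.
3. Only the last case is a problem, and only if such forms are accepted. The article neither accepts nor refuses them.

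**Size, for illustration only**

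The plan gives no figure for late returns or for any reporting shift, so there is nothing to reproduce. Assume that a share f of the analysed IPSS scores in an arm was completed after disclosure, and that knowledge moves those scores by b units. The bias in the mean difference is then

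bias = f × b (one arm shifts), or 2 × f × b (both arms shift by b, in opposite directions, with the same f).

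The margin comes from the Sample size section: "We have specified differences of 4 ml/s in Qmax and 2.5 units in IPSS, as demonstrating equivalence".

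| f (assumed) | b (assumed) | One arm | % of 2.5 | Opposite directions | % of 2.5 |
|---|---|---|---|---|---|
| 5% | 2 | 0.05 × 2 = 0.10 | 4% | 0.20 | 8% |
| 10% | 3 | 0.10 × 3 = 0.30 | 12% | 0.60 | 24% |

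With the planned 163 completers per group, f of 5% to 10% means about 8 to 16 men per arm (0.05 × 163 = 8.15; 0.10 × 163 = 16.3).

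**What such a bias would do to the IPSS equivalence test**

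Inputs from the Sample size section are SD 5, n = 163 per group, margin 2.5 and assumed true difference 0.4. I take the 95% confidence interval as two one-sided tests at 0.025. The standard error is 5 × √(2/163) = 0.554. With m the margin and d the true difference plus bias, the normal approximation gives

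P(declare equivalence) = Φ((m − d)/SE − 1.96) + Φ((m + d)/SE − 1.96) − 1.

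| Bias (units) | Power if the bias adds to the 0.4 difference | False equivalence if the true difference is 2.5 and the bias is toward zero |
|---|---|---|
| 0 | 96.6% | 2.5% |
| 0.10 | 95.0% | 3.8% |
| 0.20 | 92.9% | 5.5% |
| 0.30 | 90.1% | 7.8% |
| 0.60 | 77.3% | 19.0% |

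The zero-bias power of 96.6% is above the article's stated value of just over 90%. That difference is not part of this point; the row serves only as the baseline for the rows below it.

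**The case against.** The strongest reply is that the second trigger marks the end of the wait: a man is reminded, given a month, treated as a non-responder and then told. On that reading no later form would be used, and the closing rule may stand in the full protocol or the analysis plan, neither of which is shown. This is a fair reading, and the harm does depend on late forms being accepted. But the article ties disclosure to the passing of time and not to closure of the form, so its wording does not secure that outcome.

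A second reply is that blinding was openly partial, since GPs may disclose and awareness is asked about. That stands as a limit on how much is lost. It is weaker as a defence of the rule, because disclosure by the trial itself is the one route the trial fully controls.

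Three stronger readings are tempting and are not supported:

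- **That unblinded forms would go unnoticed.** The 12-month questionnaire asks when and how the man became aware, so a form completed after disclosure carries its own marker, subject to recall. What is absent is a listed analysis that uses it, and the analysis plan may yet supply one.
- **That the trial keeps chasing men after telling them.** The Sample size section plans reminders by letter, text and telephone. It does not say that they are repeated or that they continue after disclosure.
- **That the 20% allowance shows late returns to be common.** That figure is loss to follow-up, meaning men without 12-month data, and the article calls it conservative. It says nothing about men who return a form late.

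**Conclusion.** The point holds in a limited form. As worded, the rule lets the trial disclose allocation while the co-primary IPSS is still outstanding, which works against the section's own aim of reducing assessment bias. Forms completed in clinic and forms returned within the month are not unblinded by this rule, some reminders will concern only the diary, and Qmax, as a flow measurement, is little affected.

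The size is unknown. Under the assumed inputs the bias is 0.10 to 0.30 units if one arm shifts and 0.20 to 0.60 if the arms shift in opposite directions. The upper end needs a tenth of all forms to arrive after disclosure and a shift from knowledge alone of 3 units in each arm, which is larger than the whole margin; it should be read as an outer bound of the illustration and not as an expectation. A reader might infer that the IPSS result is compromised, but the article does not support that. The likely effect is small unless late returns are common. Severity is minor, and the case for acting rests mainly on how little the remedy costs.

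**What to change.** Reword the rule so that allocation is disclosed only after the 12-month IPSS has been received, or after its collection window has been formally closed to further returns. The Bladder Diary need not hold up disclosure on account of the IPSS.

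For men already told, record the date of disclosure. Use it together with the awareness item to identify any IPSS completed afterwards. In a pre-specified sensitivity analysis, set those scores to missing and handle them with the multiple imputation already planned. Report how many there are in each arm; if there are none or very few, that alone settles the matter.

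The cost is one change to the mailing procedure, one date field and one extra analysis. The downside is that a few late responders wait longer to learn which operation they had. The article describes disclosure in the future tense and has follow-up running to the end of November 2017, so the change was still open when it was published.

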### Statistical analysis

All data analysis will be in accordance with the Consolidated Standards of Reporting Trials (CONSORT) guidelines extension for non-inferiority and equivalence trials [15]. A full statistical analysis plan will be developed and agreed by the Data Monitoring Committee and the Trial Steering Group prior to undertaking any analyses of the trial data.

Descriptive statistics will be used to compare patient baseline characteristics between the two treatment groups. The primary comparative analyses will be conducted on an ‘as allocated’ basis and will employ multivariable linear regression to investigate equivalence in Qmax and IPSS between ThuVARP and TURP at 12 months. Analyses will adjust for stratification variables (centre and retention). Interpretation of results will focus on observed differences, and 95% confidence intervals for the between-group comparisons, to determine whether clinically important differences between ThuVARP and TURP are unlikely. Missing data will be imputed using multiple imputation modelling. Additional sensitivity analysis will explore the impact of missing data by using complete cases only. Sensitivity analyses will also consider adjustment for baseline measures of Qmax and IPSS (with clinically sensible values imputed for those with retention, for example a Qmax of zero) any variables demonstrating imbalance at baseline. Consideration will also be given to surgeon effects using mixed-effects models.

As randomisation will occur close to the time of surgery, a significant cross-over between treatment groups is thought unlikely, but any departures from protocol are likely to make the treatment groups more similar. In a superiority trial an ‘as allocated’ (or intention-to-treat) analysis is a conservative approach. In an equivalence trial, such as this, where the objective is to demonstrate that treatments have a similar effect, a per protocol analysis may be a more conservative approach, but prone to bias. An alternative is randomisation-based efficacy estimators (complier average causal effect models (CACE)) which maintain randomisation [16]. If protocol deviations occur we will conduct sensitivity analyses to assist with the interpretation of the primary result, these will include CACE and per protocol analyses with discussion of any likely bias in the resulting estimates.

Analyses of secondary analyses will employ linear, logistic or multinomial regression models as appropriate. Repeated measure models will explore any treatment-time interactions considering the 6 weeks and 3 months data in addition to baseline and 12 months. Potential effect modifiers, selected a priori and informed by previous evidence, will be explored using formal tests or interaction. These will include:Clinical diagnosis at baseline of LUTS secondary to BPO or urinary retention (stratification variable)Pre-operative prostate size measured by digital rectal examinationAgePatient co-morbidities at baseline (Charlson Comorbidity Index)Conduct of TURP procedures; whether monopolar or bipolar TURPLength of stay of procedures; including whether day-case or inpatient

Interpretation will focus on the confidence intervals only and will be hypothesis-generating since the trial is not powered for such analyses. No interim analyses are planned.

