#### Clinical outcomes

Urine flow rate (Qmax), post-void residual (PVR) and voided volume (VV) were measured before surgery in men who were able to void without a catheter. The most recent existing measures were used if they were performed within 90 days of informed consent. PVR and VV were measured post-operatively, and Qmax, PVR and VV at 3 and 12 months post-surgery. These follow-up flow measures are not collected if men are catheterised, but trial without catheter (TWOC) data is recorded.

Blood parameters were also measured at baseline and post-operatively, including full blood count (FBC) and urea and electrolytes (U&Es).

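### The primary models leave the already collected baseline IPSS and Qmax to a sensitivity analysis, giving up a modest, nearly free gain in precision and correction for chance baseline imbalance

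*Protocol article*

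**What the plan says.** The Statistical analysis section of the protocol article names linear regression of Qmax and IPSS at 12 months as the primary comparison and fixes its covariates: "Analyses will adjust for stratification variables (centre and retention". These match the design, since "Randomisation was stratified by centre and whether the patient was eligible due to bothersome LUTS or urinary retention".

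Baseline values come later in the same section, under sensitivity analyses: "Sensitivity analyses will also consider adjustment for baseline measures of Qmax and IPSS". A parenthesis deals with men who have no baseline flow: "with clinically sensible values imputed for those with retention, for example a Qmax of zero". Directly after it, with no conjunction, the sentence goes on to "any variables demonstrating imbalance at baseline". The only other stated statistical use of the baseline values is in repeated-measures models of treatment-time interaction, "considering the 6 weeks and 3 months data in addition to baseline and 12 months".

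The data are there. Under Clinical outcomes, flow measures "were measured before surgery in men who were able to void without a catheter". Under Patient reported outcomes, every participant gets a baseline questionnaire, with a separate version for catheter users, "as some items were not relevant for catheterised patients".

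**The concern.** Each co-primary outcome is a 12-month value whose own baseline is already recorded, yet that baseline is absent from the model that decides the trial. Equivalence is read from the 95% CI against the margins, so the width of the interval bears directly on the answer. Stratification balances centre and presentation. Within a stratum, neither the design nor the primary model corrects for one arm happening to start with worse symptoms or slower flow. The covariate set is a stated choice in the article, so this is not a detail merely left to the SAP.

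The planned sensitivity analyses also admit covariates because they look imbalanced in the observed data, with no list and no threshold.

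**Working it through.** **Inputs from the article (Sample size).** Completers: 163 per arm. SD of 12-month values: 9 ml/s (Qmax) and 5 units (IPSS), with no reduction for baseline. Margins: 4 and 2.5. Assumed true differences: 0.4 and 0.4. Two-sided alpha 5%, so 2.5% for each one-sided test. I treat the SDs as residual SDs after centre and retention.

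**Assumptions not in the article.** 75% of men have a usable baseline. The within-stratum correlation r between baseline and 12 months is 0.2 to 0.5.

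**1. The plan's own power.** SE = SD × √(2/163), which is 0.997 ml/s for Qmax and 0.554 units for IPSS. The chance that the 95% CI lies inside the margins is Φ((m − d)/SE − 1.96) + Φ((m + d)/SE − 1.96) − 1.

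- Qmax: Φ(3.61 − 1.96) + Φ(4.41 − 1.96) − 1 = 94.4%; the plan states 85%.
- IPSS: Φ(3.79 − 1.96) + Φ(5.24 − 1.96) − 1 = 96.6%; the plan states just over 90%.

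The stated figures do not reproduce; they are lower than their own inputs imply. That is a separate matter, but it means the starting power used below is recomputed, not the plan's.

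**2. Effect of adding baseline.** Men with a usable baseline have residual variance SD² × (1 − r²); the others keep SD². With a 75% share, the average factor is 1 − 0.75r². The half-width is 1.96 × SE × √factor.

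| r | variance factor | equivalent extra patients | half-width Qmax / IPSS | power Qmax / IPSS |
|---|---|---|---|---|
| none | 1 | – | 1.95 / 1.09 | 94.4% / 96.6% |
| 0.2 | 0.970 | 3% | 1.92 / 1.07 | 95.0% / 97.0% |
| 0.3 | 0.933 | 7% | 1.89 / 1.05 | 95.8% / 97.5% |
| 0.5 | 0.813 | 23% | 1.76 / 0.98 | 97.8% / 98.8% |

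The share matters. If men in retention contribute nothing and make up 20 to 50% of the sample, the variance reduction is 2–3% at r = 0.2 and 12.5–20% at r = 0.5.

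The gain in power points would be larger if true power were as low as stated. SDs that give 85% and 90% at this sample size are 10.36 and 5.79. With a baseline for every man, power would then become 86.8% / 91.2% at r = 0.2 and 94.5% / 96.5% at r = 0.5.

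**3. Chance imbalance.** A baseline difference of 1.96 standard errors moves the unadjusted estimate by r × 1.96 × SE if every man has a baseline. For r = 0.2 to 0.5 this is 0.39–0.98 ml/s or 0.22–0.54 units. With a 75% share, multiply by √0.75 = 0.866 to get 0.34–0.85 ml/s or 0.19–0.47 units.

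**4. Does the value filled in for retention matter?** Let R indicate the retention stratum and fill the constant k for all of it. The filled baseline is then (baseline among the rest) + k × R. R is already in the model, so changing k only adds a multiple of an existing column and the treatment coefficient is exactly unchanged. If only some men in the stratum receive k, their indicator is not in the model and the result depends on k. A simulation for IPSS assumed 326 men, 25% in retention, r = 0.3, and real values for 30–50% of the retention men. Fills of 0, 10 and 35 moved the estimate by a little over 0.1 unit on average, more than the 0.04-unit gain in half-width at that r. Adding an indicator for filled-in men restored exact invariance.

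**The case against.** The strongest reply is that nothing here is invalid. The primary model adjusts for both stratification factors and is unbiased over randomisation, its CI already allows for chance imbalance on average, and baseline adjustment is planned as a sensitivity analysis. With a true difference of 0.4, the expected upper limits are 0.4 + 1.95 = 2.35 ml/s and 0.4 + 1.09 = 1.49 units, already well inside the margins. At r = 0.2 to 0.3 the power gain is only about 0.4 to 1.4 points. All of this stands and limits the point to efficiency and robustness. It does not make omitting a collected covariate the better choice.

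Some stronger readings are not supported:

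- A reader might infer that the trial is biased or underpowered because baseline is left out. The calculation shows neither.
- A reader might infer that the value filled in for retention never matters. The article links missing baseline flow to being unable to void without a catheter, not to the stratum, and catheter users may have partial questionnaire data. A mixture of real and filled values within the stratum is therefore possible.
- A reader might infer that baseline and imbalance-driven covariates go into one model. The sentence lacks a conjunction and speaks of analyses in the plural, so separate models are just as plausible.
- A reader might infer that the team may choose between two sets of results. The primary model is named in advance, so covariates picked by imbalance cannot change the primary estimate.

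**Conclusion.** The concern holds as a modest improvement worth making. The choice of centre and retention as the only primary covariates gives up some precision and leaves within-stratum chance imbalance uncorrected, when the needed data are already in hand. Under the two assumptions, the gain is worth 3 to 23% more patients and 1 to 3 points of recomputed Qmax power. At the lower correlations it is small. The direction is secure; the size is not, because the article gives neither the correlation nor the share of men with a usable baseline. Validity is not at stake.

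**What to change.** Pre-specify in the SAP, before any comparative analysis:

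- Each primary model regresses the 12-month value on arm, centre, retention and the baseline value of the same measure.
- Men in retention without a usable baseline receive one stated constant. If some men in that stratum keep a real value, add an indicator for those filled in, so that the constant cannot affect the treatment estimate.
- Other missing baselines are handled consistently with the multiple imputation already planned.
- The model with centre and retention only becomes the sensitivity analysis.
- Covariates chosen because they look imbalanced are dropped, or kept in a separate analysis labelled as secondary. The sentence that introduces them is repaired so that the models are distinct.

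The cost is wording and about one or two degrees of freedom per model; no new data or visits are needed. The article says the SAP will be agreed before any analysis and that follow-up runs to November 2017, so on its own timetable the change could still be pre-specified.
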